**Methods:**

Thirty-nine patients will be assessed at baseline (T0–18 h of coma) and randomly assigned to the PM (control group), BFRp, or BFRpE groups. The training protocol will be applied in both legs alternately, twice a day with a 4-h interval until coma awake, death, or ICU discharge. Cardiovascular safety and applicability will be evaluated at the first training session (T1). At T0 and 12 h after the last session (T2), muscle thickness and quality will be assessed. Global muscle strength and physical function will be assessed 12 h after T2 and ICU and hospital discharge for those who wake up from coma. Six and 12 months after hospital discharge, physical function and quality of life will be re-assessed.

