#### Measurement of secondary outcomes

##### Neuromuscular adaptations of muscle mass and strength

Muscle mass and quality adaptations will be assessed daily prior to the first training session (~ 12 h from the last session) and 12 h after the last training session (T2) (until 12 h prior to the coma awakening), to the predicted death or ICU discharge. The muscle mass of the VL, *rectus femoris* (RF), and anterior tibial (AT) will be measured by MT and muscle quality, by echo intensity, both analyses obtained by ultrasound images. If the patient awakes from a coma and has the appropriate cognition to collaborate in active assessments, the global muscle strength will be evaluated by the Medical Research Council (MRC) score after 12 h of T2, in the ICU and at hospital discharge. Adequate cognition will be assessed by the absence of delirium after completing the Confusion Assessment Method for Intensive Care Units (CAM-ICU) score [52].

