## Statistical analysis

After data collection, participants will be distributed into subgroups by periods in coma (2, 3–4, 5–6 days), in alertness (1–2, 3–4, 5–6 days), and in ICU permanence (3–4, 5–6, 7–8, 9–10, 11–12 days). The normality of data will be analyzed using the Shapiro-Wilk test. One-way analysis of variance (ANOVA) will be used for intra-group comparisons in T0. A mixed-model analysis will be used for each dependent variable, whereas group and time will be considered as fixed factors and subject as the random factor. In case of significant *F*, the Tukey adjustment will be applied for multiple comparisons. In the event of a non-normal data distribution, a Kruskal-Wallis test will be applied to test for the differences in baseline values and the Friedman test to analyze the repeated measures. The adjusted *p* values will be calculated using the Hommel procedure [48]. Effect sizes between and within groups will be calculated using Cohen’s *d* [89]. The minimal clinically important difference will be assessed with distribution-based methods [90]. The statistical significance will be assessed at *p* < 0.05. All analyses will be performed using R 3.6.2 (The R Project for Statistical Computing, 2019) in R-studio 1.3.443 (RStudio Inc., Boston, MA, USA).

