Regarding the trial design, the inclusion of patients within the first 18 h of coma identification was suggested to promote a higher experimental control. The aim of this was to ensure that there would be enough time to perform the admission procedures and the first training session, before the beginning of the deleterious effects associated with low mobility [15, 16].

Another control that was adopted was the randomization of patients into experimental groups by ranking the characteristics that could impair the between-group comparison. More specifically, a peculiar aspect of intensive care studies is the high variability of the sample characteristics, principally in adult ICUs, where the admission involves non-pediatric patients of both sexes, with all types of clinical severe illness, pre- and post-surgery. Thus, to homogenize the experimental groups, we purposely stratified the participants into quartiles, considering MT and type of disease.

To further enhance trial control, our study also proposed daily assessments involving muscle mass. This strategy enables a detailed and trustworthy monitoring of the training-related responses, which differs from specific evaluations, performed during the pre- and post-training period. In addition, this strategy may be important for the experimental and statistical adequacy of the clinical trial to intensive care, in which daily pre- and post-session assessments allow lower experimental losses. Thus, in the event of unanticipated patient discharge or death, the statistical analysis may include the last assessment data from the previous day.

Despite the positive aspects presented, the study is not without limitations. The inclusion of patients with varied duration of coma (2–6 days of intervention and 2 to 12 days of ICU permanence) may lead to high heterogeneity at both time points. As an alternative, the use of subgroups for the duration of the coma (2–3, 4–5, and 6 days), alertness (1–2, 3–4, and 5–6), and the time of stay in the ICU (3–4, 5–6, 7–8, 9–10, and 11–12) was suggested. Finally, the patients who were not classified in the study groups or in the added subgroups should be included in the clinical trial flowchart, but not in the statistical analysis.

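### For daily muscle scans, a mixed model with subject as its only random factor makes the arm-by-time test too liberal if all daily scans are analysed and wasting rates differ between patients

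*Protocol article*

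**What the plan says.** The Statistical analysis section sets a single approach: "A mixed-model analysis will be used for each dependent variable", where "group and time will be considered as fixed factors and subject as the random factor". It names no random slope and no residual correlation, and it does not write out the group-by-time term. Tukey and Hommel adjustments follow, and "The statistical significance will be assessed at *p* < 0.05".

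The article describes the scan schedule in two ways. The section on neuromuscular adaptations says "Muscle mass and quality adaptations will be assessed daily prior to the first training session", with a further scan 12 h after the last session. The Discussion supports daily scanning over a pre/post comparison: "This strategy enables a detailed and trustworthy monitoring of the training-related responses". The abstract's Methods paragraph gives two time points only: "At T0 and 12 h after the last session (T2), muscle thickness and quality will be assessed". The Discussion adds that the previous day's scan may be used when a patient is discharged or dies unexpectedly.

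Table 1 admits patients with a predicted coma of 2 to 6 days. The sample is 39 patients in three arms.

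**The concern.** The muscle hypotheses in the Background (BFRp reduces atrophy, BFRpE prevents it) are about differences in change between arms, so they rest on the arm-by-time comparison. A random intercept lets patients differ in level but assumes that everyone in an arm changes at the same rate, apart from scan error. If rates differ, that spread goes into the residual. It is then averaged over all scans, when it should be averaged over about 13 patients per arm. The standard error of the arm difference in change becomes too small, and the test can credit an arm with slowing atrophy when the arms do not differ. The Tukey and Hommel adjustments start from the same standard errors and do not correct this. The abstract says the data will inform the design and sample size of a later trial, so overstated precision would carry forward.

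**Working it through.** **Inputs from the article.** 39 patients in three arms, taken as 13 per arm; nominal level 0.05; coma of 2 to 6 days, taken as T0 plus one scan per day, so 3 to 7 scans; time as a factor, hence categorical.

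**Inputs assumed.** The article gives no standard deviation (SD) for wasting rate or for scan error. What matters is the ratio r = (between-patient SD of daily change) / (scan-error SD), varied from 0 to 2.

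**Model as stated.** Y_ij = arm + time + arm×time + u_i + e_ij, with one random term u_i per patient. The null simulations add a patient-specific slope b_i × day and no arm effect.

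**Reproducing the stated 5%.** With r = 0 the test rejects in 4.7% to 5.2% of trials with time as a factor, so the model is correct when wasting rates are equal within arms.

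**False-positive rate of the arm-by-time F test** (random intercept, time as a factor, 13 per arm, 10,000 runs per cell):

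| Scans analysed | r = 0.25 | r = 0.5 | r = 1 | r = 2 |
|---|---|---|---|---|
| T0 and T2 only | 5.1% | 4.8% | 4.9% | 5.0% |
| 5 daily scans, all patients | 5.3% | 7.2% | 11.0% | 14.3% |
| 7 daily scans, all patients | 6.1% | 11.1% | 15.7% | 17.2% |
| 3 to 7 daily scans, varying | 8.8% | 16.5% | 27.4% | 30.8% |

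Results with 10 per arm are similar. A restricted maximum likelihood (REML) random-intercept fit of the varying schedule (250 runs per cell) gave 7.6%, 20.8% and 31.2% at r = 0.25, 0.5 and 1, so the table is not an artefact of the simpler F computation.

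**Analytic check of the balanced rows.** With k scans the nominal test uses 2(k−1) and 36(k−1) degrees of freedom. When slope spread dominates, only one contrast per patient carries the variation, so the true reference is F(2, 36), and P(F(2, 36) > c) = (1 + 2c/36)^(−18).
- k = 7: the 5% critical value of F(12, 216) is c = 1.797. The rate is (1.0998)^(−18) = 18.0%, the ceiling that the 17.2% approaches.
- k = 5: the critical value of F(8, 144) is c = 2.003. The rate is (1.1113)^(−18) = 15.0%, against 14.3%.
- k = 2: nominal and true degrees of freedom are both (2, 36), so the rate is exactly 5%. Each patient supplies one change score, and its between-patient variance is the residual.

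**If day were entered as a linear term**, the varying schedule gives 19.5%, 39.3%, 56.0% and 61.6% across the four ratios. The article calls time a factor, so these are not the main result.

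**Alternatives.** One-way ANOVA on per-patient slopes rejects in 4.4% to 5.6% in every cell. A REML random intercept and slope on the varying schedule rejects in 0.8% to 4.4% with categorical time and 6.0% to 7.2% with linear time (Monte Carlo error about 1.4 points).

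**The case against.** **The daily scans may not all be modelled.** The abstract names only T0 and T2, and the Discussion partly uses daily scans as a back-up for a missed final one. This stands: under a T0/T2 analysis there is no inflation. But the Discussion also presents daily scanning as serving the statistical adequacy of the trial, so modelling every scan is a fair reading.

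**The wording is shorthand, and covariance detail may sit in an analysis plan that is not shown.** It does not exclude a random slope. Even so, the article commits to a structure for every outcome and names time only as fixed. The point concerns that stated choice.

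**The size is assumed.** This stands. With slope SD 0.5 and error SD 3 (r about 0.17), the rate is 6.6% with varying follow-up and 4.9% with six days for all. The article's remark that "a peculiar aspect of intensive care studies is the high variability of the sample characteristics" concerns patient mix and justifies stratified allocation; it gives no information on wasting rates.

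**The plan has coma-duration subgroups.** These equalise follow-up, not wasting rates. With an assumed 4 per arm in each subgroup, the rates are about 6% at slope SD 0.5 and error SD 2, and 4%, 8% and 12% at slope SD 1. That lessens the problem but does not remove it.

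**Stronger readings.** A reader might infer that serial scans count as nearly independent evidence. They do not: with an assumed baseline SD of 15 and error SD of 2, the random intercept implies a within-patient correlation of 225/229 = 0.98. Only correlation in change is ignored. A reader might also infer that error rates are certain to be well above 5%, or that the arm estimates are biased. The documents support neither; the mechanism shrinks standard errors.

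**Conclusion.** The point holds conditionally. The stated model is correct if wasting rates are equal within arms, and harmless if only T0 and T2 are analysed. If all daily scans enter it and rates differ, the arm-by-time test for muscle thickness and echo intensity is too liberal: about 5% to 9% at r = 0.25, up to about 30% at r = 1 to 2 with varying follow-up, against a nominal 5%. This rests on 13 per arm, time as a factor, 3 to 7 scans per patient and assumed variance ratios. The article does not allow a choice within that range. Because these are secondary outcomes of a pilot, the change is worth making but is not critical to the primary safety and applicability objectives.

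**What to change.** In the Statistical analysis section, state for muscle thickness and echo intensity whether all daily scans or only T0 and T2 are modelled, and bring the abstract into line.

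If all daily scans are modelled, replace the single random factor for these outcomes with one of the following:
- a patient-level random intercept and random slope for day since T0, or an unstructured within-patient covariance, with small-sample degrees of freedom such as Kenward-Roger;
- as the simple option at 39 patients, a comparison between arms of each patient's own change per day, also named as the fallback if the larger model does not converge.

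A first-order autoregressive structure should not be offered as equivalent unless it is shown to restore 5% when slopes vary.

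The cost is one or two sentences and a changed model call in R, with no new data, patients or procedures. The downside is wider confidence intervals and possible non-convergence, which the per-patient comparison covers.

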### Study population

The inclusion, non-inclusion, and exclusion criteria are shown in Table 1. All the criteria will be reevaluated before each training session, according to the clinical specificity of the criteria (Table 1). All non-included patients will be re-evaluated after 18 h of coma, except for patients whose hospitalization is longer than 18 h prior to ICU admission. In conclusion, all patients will be assisted by the ICU physiotherapy team. Additionally, the number of PM sessions or any type of physical therapy intervention in the peripheral muscle will be quantified to control the total volume of stimulus for each patient.

**Table 1 Tab1:** Inclusion, non-inclusion, and exclusion criteria of the study population

Inclusion criteria	Non-inclusion criteria	Exclusion criteria
1. Age of 25 to 55 years	1. Persistent arrhythmia with atrial fibrillation	1. Obese (BMI > 30 kg/m^2^)
2. Scores − 5 or − 4 according to the Richmond Agitation-Sedation Scale (RASS) or 3 to 5 in the Glasgow Comatose Scale	2. Pre-existing atrioventricular block or ventricular tachycardia	2. More than one thromboembolism risk factor
3. Maximal 18 h of coma in ICU admission or during critical care hospitalization	3. Recent acute myocardium infarction	3. Previous venous thrombosis and/or pulmonary embolism
4. Prediction of coma length between 2 and 6 days	4. Provisional or definitive pacemaker	4. Peripheral arterial vascular disease history or suspicion of lower limb arterial insufficiency
5. Prediction of 2 to 12 days of ICU permanence	5. Signals of intracranial hypertension	5. Severe cardiovascular instability and/or use of vasoactive drugs in infusion ≥ 0.5 mcg/kg/min
6. Daily protein consumption standardized for the ICU medical and nutrition teams	6. Neoplasia in chemotherapy treatment	6. Deep coagulopathy (prothrombin time (PT) > 2.5 times the normative values, activated partial thromboplastin time (APTT) > 2 times the normal or platelet count ≤ 50.000/μl)
	7. Non-consolidated fractures	7. Heparin intravenous infusion ≥ 2 UI/ml
		8. Fever or hypothermia
		9. Anemia
		10. Neurodegenerative disease
		11. Musculoskeletal disease

*ICU* intensive care unit

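### The mixed model names no group-by-time term and no allocation factor, and T2 pools patients with different lengths of exposure

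*Protocol article*

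**What the plan says.** All references are to the Protocol article.

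- **Model.** In Statistical analysis, one mixed model serves each dependent variable: "group and time will be considered as fixed factors and subject as the random factor". Tukey comparisons follow a significant F, but which F is not stated. For non-normal data, Kruskal-Wallis is used at baseline and Friedman for the repeated measures.
- **Allocation.** Randomization procedures classifies patients by quartile of vastus lateralis thickness and by type of critical disease. Neither appears in the model.
- **Timing of muscle measurements.** The abstract's Methods give two occasions: "At T0 and 12 h after the last session (T2), muscle thickness and quality will be assessed". The section on neuromuscular adaptations gives a daily schedule: "Muscle mass and quality adaptations will be assessed daily prior to the first training session". Statistical analysis does not say which time levels enter.
- **End of training.** Training runs "until coma awake, death, or ICU discharge", and Table 1 admits patients by "Prediction of coma length between 2 and 6 days". T2 therefore falls on a different day for different patients.
- **Unanticipated death or discharge.** According to the Discussion, "the statistical analysis may include the last assessment data from the previous day".
- **Varied duration.** Statistical analysis says that "participants will be distributed into subgroups by periods in coma (2, 3–4, 5–6 days", with further bands for alertness and ICU stay. The Discussion proposes "the use of subgroups for the duration of the coma (2–3, 4–5, and 6 days". It also lists varied duration as a limitation and keeps patients who fall outside the groups or subgroups out of the analysis.

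**The concern.** The hypotheses at the end of the Background are that BFRp reduces atrophy and BFRpE prevents it, so the arms should change differently from T0. In a repeated-measures model that is the group-by-time contrast, or a comparison adjusted for T0. The text commits to a model structure and names neither. The non-normal branch has the same gap, since a Friedman test is within-subject and Kruskal-Wallis is assigned only to baseline. Whoever runs the model as written could report the group F as the treatment test.

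The T2 label is a separate weakness. Muscle loss builds up with days of immobility, so a T2 reading depends on how long the patient stayed in the protocol as well as on the arm. If an arm wakes, dies or is withdrawn for safety sooner or later than another, part of the T2 difference is a difference in duration.

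**Working it through.** **Inputs.** Sample size rationale gives 30 and 39 patients, hence 10 and 13 per arm if allocation is equal. It gives no effect size, SD or correlation, so the plan has no figure to reproduce on this point. Alpha is 0.05, taken as two-sided. Assumed: a T2 difference of 1 SD, equal variances, and T0–T2 correlation r from 0.5 to 0.9.

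**1. What each test estimates (T0 and T2, true T2 difference d = 1 SD).**

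- Group main effect: (0 + d)/2 = 0.5 SD, with standardised size 0.5/√((1+r)/2).
- Group-by-time (difference in change): d = 1 SD, with standardised size 1/√(2(1−r)).
- T0-adjusted: d = 1 SD, with standardised size 1/√(1−r²).

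| r | Main effect | Interaction | T0-adjusted |
|---|---|---|---|
| 0.5 | 0.577 | 1.000 | 1.155 |
| 0.8 | 0.527 | 1.581 | 1.667 |
| 0.9 | 0.513 | 2.236 | 2.294 |

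Sample-size ratios are the squared ratios of these sizes. T0-adjusted against main effect: 4, 10 and 20. T0-adjusted against interaction: 2/(1+r) = 1.33, 1.11 and 1.05, a saving of (1−r)/2 = 25%, 10% and 5%.

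The halving does not depend on having only two occasions. If daily values enter and the arms diverge linearly from day 0 to day D, the average effect is (0+1+…+D)/(D+1) = D/2 days' worth, again half the final-day effect. For T1 haemodynamics with three phases (rest, exercise, after), an equal effect in the last two is averaged to two-thirds.

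**2. Power, normal approximation, d = 1 SD.** Power = Φ(estimate/SE − 1.96), with SE = √(2/n) × √((1+r)/2), √(2(1−r)) or √(1−r²) respectively.

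| n per arm | Test | r = 0.5 | r = 0.7 | r = 0.9 |
|---|---|---|---|---|
| 13 | Main effect | 31% | 28% | 26% |
| 13 | Interaction | 72% | 91% | >99% |
| 13 | T0-adjusted | 84% | 95% | >99% |
| 10 | Main effect | 25% | 23% | 21% |
| 10 | Interaction | 61% | 82% | >99% |
| 10 | T0-adjusted | 73% | 88% | >99% |

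A check with 400 simulated two-arm trials (13 per arm, loss 0.06 against 0.03 cm/day, baseline SD 0.4 cm, reading error SD 0.05 cm) had a true mean T2 difference of 0.03 × 4 = 0.12 cm. The fitted group main effect averaged 0.049 cm (expected 0.06; simulation error 0.155/√400 = 0.008), the interaction 0.121 cm and the T0-adjusted estimate 0.120 cm.

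**3. Variable T2.** Assumed: coma length uniform on 2–6 days (SD √2 = 1.41 days), reading error SD 0.05 cm, and loss of 1–3% per day of an assumed 2 cm, which is 0.02–0.06 cm/day.

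- No treatment effect and no effect on coma length: the mean T2 contrast is zero (simulated 0.000 cm). Variable timing alone does not bias it.
- Noise, 13 per arm: variance of a patient's change = (rate × 1.41)² + 2 × 0.05². At 0.06 cm/day this is 0.0072 + 0.0050 = 0.0122, so SE = √(2 × 0.0122/13) = 0.043 cm (0.044 simulated). At 0.02 cm/day it is 0.0008 + 0.0050 = 0.0058, SE 0.030 cm. Without duration spread the SE is √(2 × 0.0050/13) = 0.028 cm.
- Chance imbalance in mean duration between two arms: SD 1.41 × √(2/13) = 0.55 days, or 0.63 days with 10 per arm.
- Estimand: with loss 0.06 against 0.03 cm/day, the difference is 0.06 cm at day 2, 0.18 cm at day 6 and 0.12 cm pooled.
- Bias if an arm shifts mean time to last session by 0.4 days: 0.4 × 0.02 to 0.4 × 0.06 = 0.008–0.024 cm, with no true effect.

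**4. The duration bands side by side.**

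| Section | Band 1 | Band 2 | Band 3 |
|---|---|---|---|
| Statistical analysis | 2 days | 3–4 days | 5–6 days |
| Discussion | 2–3 days | 4–5 days | 6 days |

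Patients with 3 days of coma, or with 5, have different companions in the two schemes. Either way, 13 per arm over three bands is about four patients per arm per band.

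**The case against.** The strongest reply is that the text does not call these the only terms. Listing the factors of a repeated-measures model without writing out their interaction is common shorthand, a journal article condenses the full plan, and effect sizes are planned both between and within groups. That stands as far as it goes: the plan may intend the interaction. The written sentence still fixes a structure, and neither it nor the non-normal branch identifies the test of differential change.

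Four stronger readings are tempting, and the document does not support them.

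- **T0 is ignored.** T0 thickness and echo intensity can enter as a level of time. Omitting T0 as a covariate costs some precision and causes no bias.
- **Ten times the patients are needed.** That ratio compares a main-effect test with a T0-adjusted one at r = 0.8. Against the interaction the saving there is about 10%.
- **The effect is confounded with duration.** Randomisation balances duration in expectation. Bias needs an arm to alter time to last session.
- **The daily ultrasound is not used as a trajectory.** Statistical analysis does not define the time levels, so the use is unspecified.

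The authors also acknowledge the heterogeneity and plan subgroups for it. The previous day's value is a real observation; the harm comes only from treating it as T2. Finally, this is a pilot whose primary cardiovascular responses are recorded at T1, so T2 timing does not touch them.

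**Conclusion.** The point holds in limited form and should be corrected. The model as written does not name the term that carries the treatment effect and leaves out both allocation factors. The size depends on the reading: under main effects the estimate is halved and power falls to about 21–31% for an assumed 1-SD effect; if the interaction is implied, the remaining gain from T0 adjustment is 5–25% of the sample size for r from 0.9 to 0.5. Because the model applies to every dependent variable, this part reaches the primary T1 haemodynamics.

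Variable T2 affects the muscle outcomes. Under the assumed loss rates it raises the SE from 0.028 to 0.030–0.043 cm, and it makes the pooled effect an average over durations. It becomes bias only if arms differ systematically in time to last session, which awakening, death or safety withdrawal could bring about. The subgroups do not solve this: they condition on a variable observed after randomisation, are defined in two conflicting ways, and come with exclusion of unclassified patients. All sizes rest on assumed correlations, effects and loss rates, since the article gives none.

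**What to change.** - **Muscle thickness and echo intensity.** Model the post-baseline daily values at their actual day since T0. Fixed effects: group, day, group-by-day, T0 value and disease type. Random intercept per patient, with a random slope only if it can be estimated. T0 enters once, as a covariate, and not also as an outcome row. Report the between-arm differences in change per day.
- **Last values.** Analyse each value on the day it was taken, and do not relabel an earlier day's value as T2.
- **T1 haemodynamics.** Use group, phase (during and after exercise) and group-by-phase, with the resting value as covariate.
- **MRC and PFIT.** These have no T0 value, because the patient is comatose; adjust for disease type only.
- **Duration bands.** With actual day in the model they are not needed for this purpose. If kept as description, the two sets must be reconciled, and falling outside a band should not remove a patient from the main analysis.

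The cost is statistical wording; the measurements are already planned. There are limits. With 10–13 patients per arm the random slope may have to be dropped and disease type kept to few categories. A linear trend also does not remove informative ending by death or awakening, so time to last session should be reported by arm beside the result.

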### Secondary objective

The secondary objective is to investigate the effects of this intervention on neuromuscular adaptations, physical function, and quality of life of ICU coma-surviving patients.

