### Quality of life assessment

#### Quality of life using the SF-36 questionnaire

Quality of life will be assessed using the SF-36 questionnaire, an instrument of good acceptance, reliability, and validity for ICU patients validated in Brazil and easily administered by telephone [45, 46, 53, 54]. It comprises 8 domains: physical function, role-physical, bodily pain, general health, vitality, social functioning, role-emotional, and mental health. Scores range from 0 to 100, where 0 corresponds to the worst general health status, and 100 corresponds to the best health condition [86–88]. The categorization and description of the methods and analyses are shown in Table 2.

**Table 2 Tab2:** Categorization and description of the methods and analyses of the study variables

Evaluation category	Organic responses	Method of evaluation	Variables in analyses
Safety and applicability	Acute cardiovascular	Pulse wave analysis (PWA)	MAP, SBPc, SBPp, DBPc, and DBPp (mmHg)
Safety and applicability	Acute cardiovascular	Analyses of the vital signs	HR (bpm) and SpO_2_ (%)
Muscle systems	Muscle mass adaptation	Ultrasound image	Muscle thickness (cm)
Muscle systems	Muscle quality adaptation	Ultrasound image	Echo intensity (A. U. from 0 to 256)
Neuromuscular systems	Global muscle strength adaptations	Medical Research Council (MRC) Score	Number scoring (0 to 60)
Physical function	Adaptations in physical function in ICU	Physical Function in the Intensive Care Test Scored (PFIT)	Number scoring (0 to 12)
Physical function	Adaptations in physical functional performance after hospital discharge	Performance in the basic activities of daily living by the Barthel Index (BI) by telephone interview	Number scoring (0 to 100)
Clinical outcomes	Adaptations in quality of life	Medical Outcome Study 36 – Item Short Form Health Survey (SF-36) questionnaire	Number scoring (0 to 100)

*SBPc* central systolic blood pressure, *SBPp* peripheral systolic blood pressure, *DBPc* central diastolic blood pressure, *DBPp* peripheral diastolic blood pressure, HR heart rate, *MAP* mean arterial pressure, *SpO*_*2*_ peripheral oxygen saturation, *ICU* intensive care unit

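### If normality is rejected, the planned fallback contains no test between the three arms after baseline

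*Protocol article*

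**What the plan says.** All the rules at issue stand in the Statistical analysis section of the protocol article.

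- Trigger: "The normality of data will be analyzed using the Shapiro-Wilk test".
- Default: one mixed model per dependent variable, in which "group and time will be considered as fixed factors and subject as the random factor", with Tukey comparisons after a significant F.
- Fallback for non-normal data: "a Kruskal-Wallis test will be applied to test for the differences in baseline values and the Friedman test to analyze the repeated measures".
- Multiplicity: adjusted p "values will be calculated using the Hommel procedure".
- Effect sizes: "Effect sizes between and within groups will be calculated using" Cohen's d.
- Significance threshold: p < 0.05.

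The question to be answered is set elsewhere. The Secondary objective is to "investigate the effects of this intervention on neuromuscular adaptations, physical function, and quality of life" in survivors. The hypothesis at the end of the Background is explicitly between arms: it expects BFRpE to do better than BFRp on physical function and quality of life. The Discussion describes the design as between-subject.

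**The concern.** The default analysis has a group factor and the fallback does not, apart from a comparison of baseline values. An outcome that fails the normality check therefore moves from an analysis that can address the treatment question to one that cannot. Every outcome type is exposed: muscle thickness, echo intensity and the cardiovascular variables as well as MRC, PFIT, Barthel and SF-36.

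Two things are at stake. The between-arm hypothesis could go untested for those outcomes. And a significant Friedman result, which says only that values changed over time, could be reported as if it showed an effect of the intervention.

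**Working it through.** The plan states no figure to reproduce here. The check is what the named tests can detect, followed by a simulation and a look at how often the trigger would fire.

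**1. What each fallback test compares.** Friedman ranks each patient's own values across the k visits and sums the ranks by visit:

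Q = 12/(n·k·(k+1)) · ΣR_t² − 3n(k+1).

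With n = 30 (the number used in the Sample size rationale) and k = 3, this is Q = ΣR_t²/30 − 360. No arm label enters. Reassigning patients to other arms leaves Q unchanged, and so does adding a constant to every value of every patient in one arm.

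Kruskal-Wallis does compare arms, but the plan assigns it to baseline values. By outcome, that leaves:

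| Outcome | Value at T0? | Arm test left in the fallback |
|---|---|---|
| Muscle thickness, echo intensity, cardiovascular variables | Yes | Before treatment only |
| Barthel, SF-36 | Yes, answered by the legal representative (Recruitment procedures) | Before treatment only |
| MRC, PFIT | No, first taken 12 h after T2 (Measurement of secondary outcomes) | None |

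Hommel adjusts p values and supplies no contrast. Cohen's d is an effect size, not a test.

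**2. Simulation.** Three arms of 10, three visits, outcome = exp(0.7·y), where y is the sum of a patient effect (SD 1), an error (SD 1), an arm shift, a time trend and an arm slope; 4,000 runs, threshold 0.05. All of these values are assumptions, since the document gives no means or SDs. Friedman was run pooled over arms, and also within each arm at 0.05/3, counting any rejection. The comparator is Kruskal-Wallis across arms at the last visit.

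| Scenario | Friedman pooled | Friedman, any arm | Kruskal-Wallis, last visit |
|---|---|---|---|
| No effect of any kind | 5.6% | 3.8% | 5.4% |
| Arms differ by 0/1/2 at every visit | 5.9% | 3.6% | 72.8% |
| Arms differ by 0/2/4 at every visit | 4.9% | 3.5% | 99.98% |
| Same trend 0/1/2 in all arms, no treatment effect | 99.98% | 97.5% | 4.5% |
| Opposite arm slopes −1/0/+1 | 1.4% | 92.7% | 99.98% |

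The rows with a constant arm difference are the relevant picture for MRC and PFIT, whose visits all fall after treatment: Friedman stays at about its false-positive rate whatever the arms do. The common-trend row shows the reverse error. Running Friedman arm by arm does not rescue it, because it rejects in 97.5% of trials under a shared trend with no treatment effect.

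**3. How often the fallback would be used.** Shapiro-Wilk at 0.05 on rounded scores clipped to the scale, n = 30, 5,000 runs:

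| Score | Assumed mean, SD near ceiling | Trigger | Assumed mean, SD mid-scale | Trigger |
|---|---|---|---|---|
| PFIT (0–12) | 9, 3 | 74% | 6, 2.5 | 11% |
| MRC (0–60) | 48, 12 | 60% | 40, 10 | 5% |
| Barthel (0–100) | 90, 25 | 99.5% | 70, 20 | 15% |
| SF-36 (0–100) | not run | – | 50, 20 | 4% |

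The plan does not say whether normality is checked pooled or by arm. At n = 10 the near-ceiling rates fall to 19% (PFIT), 16% (MRC) and 60% (Barthel).

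**The case against.** The strongest reply is that the gap is conditional. The mixed model with group is the default for every outcome and stays in force wherever Shapiro-Wilk does not reject, and a between-group Cohen's d is planned in either case. This stands. A reader might infer that strength, function and quality of life would get no treatment comparison at all. The document does not support that: what is missing is a between-arm test, and only for outcomes sent to the fallback. Nor does it support saying that most bounded scores will be sent there, because the trigger rate depends on where the scores lie.

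A reader might also take muscle loss as proof that Friedman would be significant in every trial. With 13 per arm, SD 0.2 of the baseline mean and within-patient correlation 0.90 or 0.95, a common 10% loss does make Friedman reject in about 100% of trials. But that figure rests on the assumed loss: with 3% it is 32% (correlation 0.90) or 18% (0.80). Those simulated data are also Gaussian, so Shapiro-Wilk would reject in only about 5% of trials and the mixed model would normally be used.

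Friedman needs complete series, which might suggest that every patient with a missing visit is lost. The Discussion allows the last assessment from the previous day to be used after unexpected discharge or death. That at least partly covers the daily muscle measures, though not the scores at 6 and 12 months.

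Finally, this is a pilot, and its decisions on safety and applicability rest on fixed percentages (15%, 20% and 5%) rather than on these tests. That limits the consequence. It does not remove the defect, since the plan sets a significance threshold and states between-arm hypotheses. Nor is this detail that a separate analysis plan would be expected to supply: the article names the replacement tests, and they cannot answer its own question.

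**Conclusion.** The fallback is wrong as written. For any outcome that fails the normality check, it leaves no hypothesis test between PM, BFRp and BFRpE after baseline, and for MRC and PFIT not even a baseline one. A significant Friedman result would not be evidence of a treatment effect. This conclusion follows from the structure of the tests and needs no distributional assumption.

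The simulated rejection rates illustrate it under assumed values. How often the fallback would apply is unknown; the assumed distributions give about 5% to 99%. The point does not touch outcomes that stay in the mixed model, or the fixed safety and applicability thresholds.

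**What to change.** In the non-normal branch, replace the baseline-only Kruskal-Wallis and the Friedman test as the analysis of treatment by:

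- for MRC and PFIT, Kruskal-Wallis across the three arms on the post-treatment value at each visit;
- for muscle thickness, echo intensity, the haemodynamic variables, Barthel and SF-36, Kruskal-Wallis across arms on the change from T0 at each later assessment;
- pairwise contrasts between arms with the Hommel adjustment already named in the plan;
- Friedman, if kept, only as a description of change within each arm.

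A rank-based method with group, time and group-by-time terms is an acceptable alternative. Dropping the normality switch, or using ordinal models for the scores, is optional; with about 10 to 13 patients per arm before deaths, ordinal models with many terms could be fragile.

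The cost is a few sentences in the Statistical analysis section, a few lines of R, and a few more tests to adjust for. No new data are needed.
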